### **FGD guide**

After providing a brief introduction to the study and intervention, collect the following information:

- a) Socio-demographic details - age, literacy status, economic status, residence (urban/rural), type of family (nuclear/extended), occupation, number of children, source of water, electrification, ownership of mobile phone, availability of cooking gas, availability of toilet facility at home and distance from the hospital.
- b) At your home who is in control of kitchen i.e. who makes the decisions related to dietary intake?

### **Theme 1: Physical activity**

- a) Explore perceptions of post-partum physical activity.
- b) Explore understanding of leisure time physical activity.
- c) Explore beliefs about adequate physical activity.
- d) Explore opportunities for exercise available and type of exercise available.
- e) Understand levels of exercise through household activities and perceptions of these being sufficient.
- c) Explore barriers to exercise (environmental or social barriers/lack of motivation/perceptions of post pregnancy weight gain).
- d) Explore potential facilitators of exercise.

### **Theme 2: Healthy diet**

- a) Explore perceptions about healthy diet (relationship to weight gain, content).
- b) Explore perceptions about post-partum diet (e.g. should be high in sugar and ghee).
- c) Explore barriers to dietary change (e.g. who makes choices about family diet?).
- d) Explore potential facilitators for dietary change.

### **Theme 3: Patient journey once diagnosed with GDM**

- a) Explore journey especially with respect to post-partum advice about future risks and how to manage these (including whether OGTT testing had been offered).
- b) Explore post-partum interactions with delivery hospital and opportunities for re-engagement.
- c) Explore concerns regarding costs or inconvenience that may be associated with post-partum care focused on mother's future health.

### **Theme 4: Postpartum screening**

- a) Explore facilitators and barriers for returning for an OGTT in the post-partum period.

### **Theme 5: Intervention**

After providing a brief introduction to the intervention:

- a) Explore reasons why women may or may not be interested in participating in the intervention.

- b) Explore potential facilitators of attendance (e.g. timing with well -baby or family planning services, providing child care).
- c) Explore preferences for size and timing of groups (day of week / time of day).
- d) Explore barriers/challenges to attend group sessions at prescribed intervals.
- e) Explore preferences for including family members / friends being involved in group sessions.
- f) Explore preference for type of health professional delivering group sessions.
- g) Explore preference for peer interactions.
- h) Preference of remote support strategies– phone call/SMS/smartphone apps and any facilitators or barriers to remote support (e.g. literacy, infrequent phone access).

**Lifestyle InterVention IN Gestational Diabetes (LIVING)****PROCESS EVALUATION PROTOCOL****Overview of the LIVING study**

The Lifestyle Intervention in Gestational Diabetes (LIVING) study is a randomised controlled trial (RCT) of a low intensity lifestyle modification programme tailored to women with GDM in India, Bangladesh, and Sri Lanka. The multiple interacting components of this complex intervention were informed by several successful studies in the prevention of T2DM and weight gain, which have been described elsewhere. The multicentre study will be undertaken over 60 months (December 2015 to December 2020). 1414 women with prior GDM will be recruited from a total of up to 24 hospitals in these three countries. The primary outcome of the randomised trial is the proportion of women with a worsening of glycaemic category at or prior to the final visit: (i) normal glucose tolerance to impaired fasting glucose (IFG) or impaired glucose tolerance (IGT) or T2DM; and (ii) IFG or IGT to T2DM. The secondary outcomes of the study include change in body weight, waist circumference, blood pressure, fasting blood glucose, physical activity level, and diet.

The intervention comprises four face-to-face group sessions, 84 automated text or pre-recorded voice messages, monthly phone calls, and two 'intensification' sessions in the event that weight goals are not achieved within six months of the commencement of the intervention. The LIVING study process evaluation conducted alongside the RCT will inform policy and decision makers about the reasons why and the mechanisms through which the intervention worked, and whether the intervention is likely to be generalisable and scalable in the real world contexts in which they work.

**Aims and objectives**

The overall aim of this process evaluation is to evaluate and understand what worked and why during the implementation of the LIVING intervention. In addition, this study aims to provide additional information that will assist in the interpretation of the LIVING study results. Specific objectives are as follows:

- i. Evaluate for whom the intervention was effective and why

- ii. Evaluate whether the intervention was implemented appropriately, and as planned
- iii. Evaluate whether the intervention is generalisable, scalable, and sustainable in a real world setting

#### Methods and analysis

Methodological approaches informing our evaluation framework

The RE-AIM framework will be used to inform the LIVING study's process evaluation framework.

The RE-AIM framework consists of five dimensions of health-related behaviour interventions: *reach* to the target population, *effectiveness* of the intervention, *adoption* by the intended recipients of the intervention, staff, and institutions such as hospitals, *implementation* (including consistency of implementation and costs), and *maintenance* of the intervention effects in specific settings over time. These five dimensions aim to encourage researchers, evaluators and policy makers to identify the elements of health interventions that improve adoption, implementation and sustainability. The RE-AIM framework was considered highly suitable as the LIVING programme was designed with the intention of broader adoption and implementation into policy and practice in the South Asian context and has been used to design our evaluation framework (Figure 1).

The LIVING study process evaluation framework

The evaluation framework (Figure 1) demonstrates each of the intervention components and the relationships among them. Firstly, the framework incorporates the intervention components addressing assumed causal mechanisms. These causal mechanisms (explained in detail in our logic model [Figure 2]) are intended to make it easier to understand why the intervention will work, and to facilitate external scrutiny of their plausibility. These assumptions are underpinned by the key elements of Michie's behaviour change wheel (capability, opportunity, and motivation). Thus, it also serves to test the applicability and robustness of the theory in the context of lifestyle change in women with prior GDM in India, Bangladesh, and Sri Lanka. Secondly, the framework incorporates implementation factors (e.g. reach and recruitment, fidelity and dose, as well as adoption and implementation), mechanisms of impact (e.g. effectiveness, acceptability, and maintenance) and finally, the outcomes of the trial (to be assessed at the end of the study).

**Figure 5.1. Evaluation framework for LIVING process evaluation**[figure not shown]**Figure 5.2. Logic model for LIVING to prevent or delay T2DM in women with GDM**

| LIVING
Intervention inputs                        | Intervention processes
and actions                                                                                                                            | Changes to capability,
motivation and
opportunity                                                                                  | Changes at
organisational
level                                                                                                                                                                            | Immediate impacts
in women with GDM                                                                                                                            | Health outcomes in
women with GDM       |
|------------------------------------------------------|------------------------------------------------------------------------------------------------------------------------------------------------------------------|------------------------------------------------------------------------------------------------------------------------------------------|------------------------------------------------------------------------------------------------------------------------------------------------------------------------------------------------------------------|-------------------------------------------------------------------------------------------------------------------------------------------------------------------|--------------------------------------------|
| Participant booklet                                  | Participants receive information regarding the health harms of GDM and the potential of lifestyle changes to prevent or delay onset of T2DM                      | Increased knowledge of health consequences triggers change to diet, exercise, and                                                        | Greater integration of departments (obstetrics and gynaecology; paediatrics; and endocrinology and diabetes) and other support staff (nursing, dietetics, and other disciplines) for improved continuity of care | More women attend postpartum screening                                                                                                                            | Prevention or delay of onset of T2DM       |
| Face-to-face group sessions                          | Participants trained to execute lifestyle change through goal-setting, self-management, and problem-solving through group sessions                               | Participants set, monitor and achieve their health-related goals                                                                         |                                                                                                                                                                                                                  | More women with GDM engage in self-care activities to improve and maintain good mental health                                                                     | Improved quality of life and mental health |
| Text or voice messages                               | Intervention facilitators reinforce new skills and knowledge through phone calls, text messages and offer intensification after personalised barriers assessment | Participants devise strategies to improve self-efficacy, and overcome physical, social, and psychological challenges to lifestyle change | Improved access to care for women with GDM due to within-system task-shifting                                                                                                                                    | More women with GDM maintain a healthy weight through changes to diet (e.g. increased consumption of fruit, vegetables, and grains; reductions in sugar and salt) |                                            |
| Motivational interviewing via telephone              |                                                                                                                                                                  |                                                                                                                                          |                                                                                                                                                                                                                  | More women with GDM exercise at least thirty minutes every day                                                                                                    |                                            |
| Intensification                                      | Group and individual sessions provide culturally appropriate social support for participants to understand GDM and make lifestyle changes                        | Motivation to maintain changes to lifestyle is sustained through text or voice messages, and phone calls                                 |                                                                                                                                                                                                                  |                                                                                                                                                                   |                                            |
| Training of auxiliary nurses to deliver intervention |                                                                                                                                                                  |                                                                                                                                          |                                                                                                                                                                                                                  |                                                                                                                                                                   |                                            |

## Methods

A mixed methods design will be used to investigate the components of our process evaluation framework. This will involve the integration of both qualitative and quantitative data in the research process including evaluation datasets, administratively collected process data accessed during monitoring visits, check lists and logs filled at intervention sites, audit reports, quantitative participant evaluation surveys, semi-structured interviews, and focus group discussions.

1. Evaluation datasets: Data from participants will be collected at randomisation, and 6 monthly intervals thereafter, with Oral Glucose Tolerance Tests (OGTT) and HbA1c tests, alternately conducted at the follow-up 6 monthly visits, and both tests at the End of Study visit.
2. Administrative data: Monitoring (at least one every six months) will be conducted by central study staff to ensure compliance with the protocol, and any local requirements. During each visit, the study monitors will fill in a monitoring report on record maintenance, conduct of sessions, and implementation of the programme, and offer feedback to ensure consistency of the implementation. The voice/text messaging report will indicate the number of successful messages sent every month as well as whether the voice message was heard completely, or disconnected early.
3. Programme checklists and logbooks: Programme specific checklists were developed in conjunction with the research team records to assess implementation fidelity, recruitment, intervention delivery, and programme context. Intervention session logs documenting attendance, collection of feedback, and participation of group members will also be analysed.
4. Programme auditing: The delivery of the group sessions will be audited by direct observation, remote observation, or audio or video recording. These data will be analysed alongside the intervention session logs and checklists. At least one of the four sessions conducted for each group will be observed by monitors. The intervention facilitators' conduct of at least one instance of each of the four different sessions will be observed by monitors.
5. Quantitative participant evaluation survey: A barriers and facilitators evaluation survey, administered after the 4th (and final) group session, at approximately 6 months after randomisation, will be undertaken to explore what women have found to be enabling and challenging in executing lifestyle modification following the group sessions. Surveys will list potential barriers to, and facilitators of, physical activity and healthy eating. Participants will also be able to list barriers and enablers that are not listed in the evaluation form.
6. Semi structured interviews: Semi-structured interviews will be conducted with a sub-group of participants, staff and stakeholders at the end of study. Interviews will also be conducted using a maximum variation sampling technique to ensure that diverse opinions are gained from healthcare workers, hospital administrators, and representatives of relevant government agencies with broad representation across the three countries.
7. Group session evaluation form: All women who attend group sessions will fill a feedback form at the end of each session. They will score their overall experience of the intervention session including feedback on intervention content, its presentation as well as facilitator's skills and behaviour.

Below, we describe how each of the data collection tools listed within the evaluation framework will be used.

### **1. Evaluating whether and how the intervention had impact, for whom and why**

#### *Surveys*

The barriers and facilitators evaluation survey and group session feedback form will help us understand what aspects of women's lifestyle are preventing them from achieving changes, and which aspects of the intervention they found useful, e.g., self-motivation, weather, scheduling, social support, or information.

The group session feedback form will explore whether the topics covered in the sessions were relevant to them, whether they felt the trainer was well prepared, whether the time allotted for the session was sufficient, and whether the content was organised and easy to follow.

#### *Evaluation datasets*

These data will be used to quantitatively evaluate effectiveness (e.g. percent change in outcome variables at the end of the trial). Data from case record forms used in initial and follow-up assessments will be used to compare characteristics of intensification and non-intensification participants to identify any trends in whom the intervention was most effective or least effective for.

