### 3.3 STUDY ARMS

#### 3.3.1 Intervention

Provisionally, the intervention will include up to 4 face-to-face group sessions combined with remote on-going support, and an intensification offering when needed (**Table 2**). However, depending on outcomes during the optimisation phase, the balance of face-to-face and remote contact might vary substantially overall, and between countries. Face-to-face sessions will be delivered by a trained facilitator using the existing HeLP-her training program optimised for each country. Eligible and consenting women will attend a local hospital in groups of not more than 10 women, and have baseline measures assessed prior to the commencement of the program. During session 1, they will receive a program-specific user manual, and over the following weeks, work through the behavioural skills sessions with a health worker trained in the delivery of the program. The participant manuals developed for the PregDiabCare pilot will undergo minor adaptation for use in each country. Following the face-to-face visits, participants will receive reminders, motivational messages, and small actionable behaviours delivered using mobile text messages and/or voice messages, which we will adapt from the WHO BE HE@LTHY BE MOBILE manual on implementing m Diabetes [30]. At week 26 from the commencement of the intervention, participants will undergo a review of progress. Program intensification will be offered to women who gain weight by the 6 month time point: those who gain >2% of baseline weight (which accounts for transient weight fluctuations) will receive two intensification sessions of individualised coaching, and monthly phone coaching for the remaining 6 months, delivered by the trained facilitators. All phases of the program focus on self-management through small, feasible, and sustainable changes, by building knowledge and skills across 3 themes (1) simple healthy eating, and moderate physical activity messages; 2) behavioural skills, such as problem-solving, goal-setting, and self-monitoring; and 3) enhancing internal motivation, self-efficacy, and self-management. Simple messages regarding eating and physical activity give women an achievable context in which to begin to formulate their own health priorities. The program is deliberately not prescriptive, and has a focus on sustainable behaviours and local context. It is estimated, based on the previous HeLP-her trials, that ~ 30% of participants may require more intensive support, as planned in the intensification sessions.

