|------------|--------------------------------------------------|--------------------------------------------------------------------|-------------------------------------------------------------------------------------------------------------------------------------------------------------------------------------------------------------------------------------------------------------------------------------------------------------------------------------------------------------------------|
|            | Session 3
Week 6                              | Group session
+
Support strategies delivered remotely | Emphasize on physical activity for a healthy lifestyle and weight management, goal setting to increase self-efficacy, and discussion on household physical activities. Group activities related to physical activity. Following this session, participants receive reminders of core messages, behaviours, and actions via SMS or voice messages and phone calls |
| Month 6    | Session 4
Week 26                             | Group session
+
Support strategies delivered remotely | Review progress. Reinforcement of previous sessions, evaluation of goal-attainment and behaviour changes made. Group activity on reviewing core messages and personal goal-setting. Participants receive reminders of core messages, behaviours, and actions via SMS or voice messages and phone calls                                                           |
| Month 7-12 | 2 Intensification Sessions (week 32 and week 44) | Individual sessions                                                | If participants are persistently overweight, or gain >2% of baseline weight, intensification is offered based on barriers' assessment done earlier, and accordingly 2 counselling sessions with monthly phone coaching and SMSs are provided.                                                                                                                           |
|            | Week 26 - 48                                     | Support strategies delivered remotely                       | Participants who lose the weight desired continue to receive reminders of core messages, behaviours, and actions via SMS and voice messages.                                                                                                                                                                                                                     |

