|            | Week 52
End of intervention evaluation        | Individual visit                                                   | Participants provide feedback on different elements of the intervention                                                                                                                                                                                                                                                                                                 |

\*From March 25, 2020, due to lockdown measures relating to the Covid-19 emergency, all intervention sessions will be held remotely (telephone or video), either individually or in groups. As weight change cannot be assessed during lockdown conditions, all participants who complete Session 4 will be offered intensification.

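### The process evaluation uses intensification status as a stand-in for non-response, so its comparison for objective (i) shows who gains weight, or who reached Session 4 under lockdown, rather than who benefited

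*Combined protocol and SAP*

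**What the plan says.** Objective (i) in Annexure 5, Aims and objectives, is to "Evaluate for whom the intervention was effective and why". Under the matching methods heading, the Evaluation datasets paragraph first plans a quantitative evaluation of effectiveness at the end of the trial. It then sets a second task for the case record form data: "compare characteristics of intensification and non-intensification participants to identify any trends in whom the intervention was most effective or least effective for". It names no control-arm comparator and no adjustment, does not say whether the group is defined by offer or by receipt, and does not mention the lockdown change.

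The rule that forms the groups is worded in three ways:

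- Protocol 3.3.1: "those who gain >2% of baseline weight (which accounts for transient weight fluctuations) will receive two intensification sessions of individualised coaching".
- Protocol Table 2: "If participants are persistently overweight, or gain >2% of baseline weight, intensification is offered".
- Annexure 5 overview: "two 'intensification' sessions in the event that weight goals are not achieved within six months of the commencement of the intervention".

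The Covid-19 footnote to Table 2 then changes the rule from 25 March 2020: "As weight change cannot be assessed during lockdown conditions, all participants who complete Session 4 will be offered intensification".

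SAP 4.9.5 separately specifies interactions between randomised group and seven baseline variables for the primary outcome. SAP 4.10 adds one by baseline glycaemic status for T2DM. Annexure 5 refers to neither.

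**The concern.** Whether an intervention works better in some women than in others is a question about the difference between arms. Intensification status cannot answer it, for three reasons.

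1. **It exists in one arm only.** Control women who would have met the weight rule are not identified, so women who gained weight despite benefiting cannot be told apart from women who did not benefit. The protocol's own Table 1 shows why this matters: in the Indian prevention trial both arms gained weight, the intervention arm less, and the lesson drawn is that benefit in South Asians can come from preventing gain. A woman who gains somewhat more than 2% but would otherwise have gained twice that has benefited, yet she counts on the least-effective side.
2. **It is built from an outcome.** Body weight is called a key secondary outcome in the synopsis. Any baseline characteristic that predicts weight gain will differ between the groups whether or not the programme does anything.
3. **Its meaning changes during the trial.** Up to 24 March 2020 it marks a weight result. From 25 March 2020 it marks reaching Session 4 by a certain date.

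What is at stake is a descriptive answer to one stated objective. Characteristics of women with a poor natural course could be reported as characteristics of women for whom the programme does not work.

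**Working it through.** The plan gives no figure to reproduce here. The check is an illustration of how far the comparison can mislead.

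**Inputs from the documents.** The trigger is a gain above 2% of baseline weight (protocol 3.3.1). About 30% are expected to need intensification (same section). The intervention arm is about 1414/2 = 707 women, so about 0.30 × 707 = 212 are intensified.

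**Assumptions, not in the documents.** Six-month weight change, in percentage points of baseline weight, is normal with SD 3 to 5. A baseline trait is present in 50% of women and adds b points of natural gain. The simple 2% rule is the only trigger.

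**Step 1: no effect in anyone.** Let a1 and a0 be the probabilities of triggering with and without the trait:

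a1 = 1 − Φ((2 − m − b)/SD), a0 = 1 − Φ((2 − m)/SD)

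The mean m is solved so that 0.5·a1 + 0.5·a0 = 0.30. The share with the trait is a1/(a1 + a0) among intensified women and (1 − a1)/(2 − a1 − a0) among the rest.

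| b | SD | m | a1 | a0 | Trait among intensified | Trait among others |
|---|---|---|---|---|---|---|
| 0 | 3 to 5 | 0.427 to −0.622 | 0.300 | 0.300 | 50% | 50% |
| 1 | 3 | −0.095 | 0.358 | 0.242 | 59.6% | 45.9% |
| 1 | 5 | −1.135 | 0.335 | 0.265 | 55.8% | 47.5% |
| 2 | 3 | −0.663 | 0.413 | 0.187 | 68.8% | 42.0% |
| 2 | 4 | −1.164 | 0.386 | 0.214 | 64.3% | 43.9% |
| 2 | 5 | −1.675 | 0.369 | 0.231 | 61.5% | 45.1% |

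Prognosis alone produces the trend. A trait that does not predict gain produces none.

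**Step 2: can the direction be wrong?** Take b = 2 and SD = 4, and let the programme reduce gain by 1.5 points with the trait and 0.5 points without it, so that women with the trait truly benefit more. With 30% triggered in the intervention arm, m = −0.114.

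| | Intervention, above 2% | Control, above 2% | Arm difference |
|---|---|---|---|
| With trait | 34.3% | 48.9% | about −15 points |
| Without trait | 25.7% | 29.9% | about −4 points |

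Within the intervention arm, the trait appears in 0.343/0.600 = 57% of intensified women and 0.657/1.400 = 47% of the others. The planned comparison points to poorer response; the two-arm contrast points correctly to better response.

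**Step 3: the lockdown rule.** If a fraction q of the arm is offered intensification under the footnote and 30% of the rest by weight, the share of the intensified group who are there under the lockdown rule is q/(q + 0.30(1 − q)). The share who would not have met the weight rule is 0.70 times that.

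| q (assumed) | Arm intensified | Present under lockdown rule | Would not have met weight rule |
|---|---|---|---|
| 10% | 37% | 0.10/0.37 = 27% | 19% |
| 20% | 44% | 0.20/0.44 = 45% | 32% |
| 30% | 51% | 0.30/0.51 = 59% | 41% |

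The documents do not give q.

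**Step 4: the other trigger wordings.** Table 2 also admits women who are persistently overweight. Under that wording, being overweight is part of the definition of the intensified group, so baseline BMI will differ between the groups by construction.

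**The case against.** The strongest defence is that the sentence seeks only trends, in an annexed and exploratory evaluation. The surveys, interviews and focus groups under the same heading also address objective (i), and SAP 4.9.5 already has the correct randomised interactions. Much of this stands, and it limits the severity. It does not rescue the sentence. Exploratory work may be imprecise, but its comparison should bear on its question, and this one can point the wrong way. Interviews explain perceptions and do not identify effect modification. Because Annexure 5 does not cite SAP 4.9.5, the two documents could give conflicting answers.

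Four stronger readings are tempting, and the documents do not support them.

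- A reader might set the weight-change gap between intensified and other women beside the 1.80 kg target difference in the synopsis. Annexure 5 compares characteristics of these groups, not their outcomes. Such a gap is not a planned contrast, and the 1.80 kg is a between-arm figure.
- A reader might infer that the comparison yields false effectiveness estimates in general. It yields no effect estimate, and misleading trends arise only for characteristics related to weight gain, to the other stated triggers, or to reaching Session 4 under lockdown.
- A reader might infer that every woman was intensified from 25 March 2020. The footnote covers those who complete Session 4, and only as an offer, so the later group is also selected on attendance.
- A reader might infer that advice on scale-up would rest on this comparison. Annexure 5 bases scalability on focus groups and stakeholder interviews, and its analysis plan triangulates across sources.

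**Conclusion.** The concern holds in a limited form. As written, Evaluation datasets treats intensification status as a proxy for non-response, and that status reflects weight course, attendance and calendar date. The sizes in the working rest on assumed SDs, an assumed trait and assumed lockdown shares. They show that the distortion can be material and can reverse direction; they do not predict what this trial will show. The conclusion itself needs none of those values, because it follows from the group being formed after randomisation, in one arm, on an outcome.

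Severity is low. The effect is confined to one exploratory process-evaluation objective. No primary or secondary estimate, test or error rate changes.

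**What to change.** In Annexure 5, Evaluation datasets:

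- Answer the for-whom question with the randomised arm-by-baseline-subgroup interactions of SAP 4.9.5, cited by section.
- Add the same interaction terms to the body-weight model of SAP 4.10.2. Label both sets exploratory in the process evaluation.
- Keep intensification only as a description of delivery and dose. State whether the group means offered or received, tabulate it by the rule in force (before versus from 25 March 2020), and draw no inference about effectiveness.
- Reconcile the three statements of the trigger in protocol 3.3.1, Table 2 and the Annexure 5 overview, so that the described group has one definition. Which wording is right is for the investigators to settle.

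The cost is a few sentences and one additional exploratory model on weight data collected in both arms; no new data are needed. The drawback is that subgroup interactions have limited power, so the answer may be inconclusive.
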